### StreetLab Protocol at UHN/KITE in Toronto

 Two dual-task paradigms will be conducted in StreetLab, a fully immersive, projection-based, VR simulator used to simulate realistic and challenging conditions (Fig. 1). StreetLab has a 240° horizontal by + 15° to -90° vertical field-of-view curved projection screen extending from the floor to ceiling. The virtual environment used in this study will depict a large urban 6-lane intersection street-crossing in Toronto. StreetLab is outfitted with an AMTI (Advanced Mechanical Technology, Inc., Watertown, MA) BP12001200–2000 strain gage force plate that measures ground reaction forces. There is a surround sound system with seven speakers (Meyersound MP-4XP; Meyersound Laboratories, Inc., Berkeley, CA) spatially distributed behind the projection screen, at approximately the height of a participant’s head when they are standing on the force plate positioned at 0**°** azimuth across a horizontal plane at ± 28° (right front and left front), ± 90° (right side and left side), and ± 127° (right rear and left rear). One subwoofer (Meyersound MP-10XP) is located in the floor under the centre speaker. All speakers are 2.14 m in depth from the participant when standing on the force plate (for more details of the acoustic properties of StreetLab, refer to [61]). Ambient traffic noise (e.g., vehicle traffic, bird noises) will be included to more closely simulate real-world acoustical conditions. The vehicle traffic will include moderate traffic density with approximately 10 cars appearing in the visual scene every 30 s. Participants will complete two dual-task paradigms that largely differ based on the two different cognitive auditory tasks to be performed, including 1) auditory 2-back task and 2) Coordinated Response Measures (CRM) task. The other primary difference from the Concordia site protocol is that instead of measuring walking as the primary mobility-related outcome measure, we will be measuring standing balance under different levels of cognitive and postural complexity.

**Fig. 1 Fig1:**
[figure not shown]
StreetLab *Note.* Participants will either stand in the centre of the force platform with a safety harness or be seated. Under dual-task conditions, participants will be standing while concurrently performing either the auditory 2-back task or the coordinated response measures task

### Auditory 2-back paradigm

*2-Back Task:* The same auditory 2-back task as the Concordia site [41] will be used; however, trials will last 60 s instead of 30 s in order to capture a sufficient amount of reliable posturography data [25]. The amplitude of the loudspeakers will be individually adjusted using an auditory 1-back task to ensure optimal audibility and comfort across participants. Specifically, participants will hear 15 untimed, single digits where they will have to repeat the digit they heard out loud to the researcher immediately after the digit is presented. In order to participate in the study, participants must attain at least 70% accuracy or higher. If the amplitude is uncomfortably loud, it will be reduced (ensuring at least 70% accuracy) and the amplitude will then be set at this level for the remainder of the experiment. Accuracy and reaction time will be measured using a handheld gaming controller (Forty4 Wireless Gaming Controller). During the main experimental task, participants will make a button press indicating whether the number they are currently hearing is the same or different than the number presented *n* steps previously (i.e., 1-step previously during the practice trials, or 2-steps previously for the 2-back task). During single-task conditions, the participants will complete the 2-back while sitting on a chair on top of the force plate within StreetLab at the same approximate eye height as standing.

*Postural Task.* Static balance will be measured by having participants stand with their feet shoulder-width apart on a force platform. In order to control for differences in hand positions across the single-task standing and dual-task trials (since participants use handheld joysticks during the 2-back task), participants will be required to hold the joystick in the same position as the dual-task trials (but will not need to make any button responses). In order to manipulate postural load, participants will complete the standing balance task with their eyes open and eyes closed. Postural measures will include spatial (centre of pressure path length; cm), temporal (velocity; cm/s) and variability (root means square, standard deviation) measures in the anterior–posterior (front and back) and medial–lateral (side-to-side) orientations.

Overall, there will be a total of six trial types: 1) single-task 2-back eyes open, 2) single-task 2-back eyes closed, 3) single-task standing eyes open, 4) single-task standing eyes closed, 5) dual-task eyes open, 6) dual-task eyes closed. Participants will complete all trial types in an ABC-CBA sequence with the three different conditions (A: single-task standing, B: single-task 2-back, and C: dual-task). This will occur two times, once for the eyes open condition, and once for the eyes closed condition. The order of trials (i.e., eyes open vs. eyes closed) will be counter-balanced across participants. DTCs (percentage) will be calculated for both the standing and 2-back tasks: [(single-task – dual-task) / single task * 100]. DTC change scores will be calculated by subtracting the post-training DTCs from the pre-training DTCs.

### CRM Paradigm

*CRM Task*: The CRM is an auditory, multi-talker task [59], which we have adapted for use in dual-task experiments in a VR environment [19, 60]. Participants will hear two simultaneously presented, but spatially distributed sentences. Each sentence will be composed of the following structure *“Ready (callsign) go to (colour) (number) now”.* A combination of 8 callsigns (Charlie, Ringo, Laker, Tiger, Arrow, Baron, Eagle, Hopper), 4 colours (red, green, white and blue) and 7 numbers (1–8 without 7) are used to compose each sentence. On each trial, a target callsign will be visually presented in text at the centre of the projection screen (e.g., Charlie). The size of a single character will be roughly 8 cm x 8 cm and the distance between the participant and the text will be roughly 2.1 m. Subsequently, two sentences will be simultaneously presented from the front speaker (0 degrees) and left speaker (- 90 degrees), one of which will contain the target word (e.g., the sentence “*Ready Charlie go to White 2 now*)”. Participants will be asked to verbally repeat the colour (i.e., white) and the number (i.e., 2) associated with the target callsign sentence. The researcher will enter the participants’ responses on a tablet (Samsung SM-T510). If the participant accurately repeats the colour and number, the trial is coded as correct and they receive feedback on the screen (“correct”) and if either the colour, the number, or both are incorrectly reported “incorrect” is presented on the screen. For each condition (see below), five listening trials/sentences will be presented within a 60 s standing trial, which will be repeated two times per condition (10 total listening trials). During single-task conditions, the participants will complete the CRM while sitting on a chair on top of the force plate within StreetLab at the same approximate eye height as standing.

In order to manipulate attentional load and listening difficulty, we will include a block of trials in which the location of the target word will be certain 100% of the time (i.e., participants will be told the target word will always be presented at 0 degrees; termed 100% trials; lower cognitive load) and a block of trials in which the location of the target word will be uncertain, presented from the centre 60% of the time and from the left 40% of the time (i.e., participants will be told that the target word will be coming from the middle 60% of the time and from the left 40% of the time; termed 60% trials; higher cognitive load). Participants will complete these 100% and 60% trial types in single and dual-task conditions.

*Postural Task*. Static balance will be measured on a force platform in a semi-tandem stance, with one foot slightly in front of the other. Postural measures will include spatial (centre of pressure path length; cm), temporal (velocity; cm/s) and variability (root means square, standard deviation) measures in the anterior–posterior (front and back) and medial–lateral (side-to-side) orientations.

Overall, there will be a total of 5 different trial types: 1) single-task CRM (100%/low cognitive load), 2) single-task semi-tandem standing, 3) dual-task (60%/high cognitive load), 4) single-task CRM (60%/high cognitive load), 5) dual-task (100%/low cognitive load). Participants will complete all trial types in this order and will then repeat the trials in the reverse order, for a total of 10 trials. DTCs (percentage) will be calculated for both the standing and CRM tasks: [(single-task – dual-task) / single task * 100]. DTC change scores will be calculated by subtracting the post-training DTCs from the pre-training DTCs.

### Secondary outcome measures

A set of secondary outcome measures will evaluate *cognitive functioning* using a series of neuropsychological tests. The Coding subtest of the Weschler Adult Intelligent Scale (WAIS-IV) will be used as a measure of visual-motor processing speed, the Digit Span subtest—forward condition will be used to measure short term memory and the Digit Span subtest- backwards condition and Letter-Number-Sequencing subtest will be used to assess auditory working memory [62]. The Trail Making Test A & B will serve to evaluate processing speed and task-switching abilities [63]. The Color Word Inference Test will be used to measure processing speed, inhibition and task-switching abilities [64]. Finally, the Rey Auditory Verbal Learning Test (RAVLT) will measure participants’ learning and retention of verbal information [65]. Different versions of the RAVLT, consisting of different word lists, will be administered at baseline and post-training in order to reduce possible practice effects. In order to determine whether participants fall within the age-normative range and can be included in the study, performance will be compared to normative data taken from the following sources: Wechsler et al., [62] for the WAIS-IV measures, Delis et al., [64] for the Color Word Interference Test, Tombaugh et al., [66] for the Trail Making Test, and Schmidt [67] for the RAVLT.

Secondary measures will also assess *sensory functioning* using a selection of visual and auditory tasks. For visual outcomes, the Pelli-Robson chart [68] will be used to assess contrast sensitivity for reading letters. For auditory outcomes, the Canadian Digit Triplets Test (CDTT) [69] will measure participants’ ability to identify digits in the presence of competing noise (i.e., their speech-in-noise perception threshold). Participants will be presented with digit triplets unaided via headphones (Telephonics TDH-39P Audiometer Headset) and asked to enter their responses into a numerical keypad (Peripad-202 HW, Perixx Computer). Pure-tone audiometry will also be conducted using a SHOEBOX Audiometer to assess participants’ hearing acuity [70]. Participants will be presented tones via headphones (RadioEar DD450) at 250 Hz, 500 Hz, 1 kHz, 2 kHz, 4 kHz, and 8 kHz at varying decibel levels in each ear. Participants will be instructed to indicate whether they can hear the tone or not by making a button response on a tablet (iPad; Apple Inc.). Performance from tones presented at the 500 Hz, 1 kHz, 2 kHz, and 4 kHz frequencies will be averaged together to create an individual PTA for the left and right ear.

A shortened version of the Balance Evaluation Systems Test called the Mini-BESTest [56] will be used to assess *motor functioning*. Postural control across four different balance control systems will be quantifiably measured, including: anticipatory transition (e.g., going from sitting to standing), reactive postural control (e.g., leaning outside one’s centre of pressure and compensating for a loss of balance), sensory orientation (e.g., balancing with eyes closed or on a compliant surface), and dynamic gait (e.g., walking while turning head, changing speed, or stepping over obstacles).

A set of questionnaires will also be given to participants to complete online using Qualtrics survey software (Qualtrics, Provo, Utah) in order to assess *subjective functioning* across cognitive, hearing, and mobility domains. Specifically, within the domain of cognition, the Frequency of Forgetting Questionnaire (FFQ) will be used to assess subjective memory abilities and how frequently one forgets things in everyday life [71]. In the domain of hearing, the Listening Self-Efficacy Questionnaire (LSEQ) will be used to assess one’s self-efficacy or confidence in understanding speech in a variety of listening situations [72], and the Hearing Handicap Inventory Screening Questionnaire for the Elderly (HHIE-S) will be given to assess self-reported experiences of hearing difficulties in everyday life [73]. Within the domain of motor functioning, the Activities-Specific Balance Confidence (ABC) Scale will be used to determine participants’ balance efficacy [74]. Additionally, participants will be asked to complete the Everyday Activity Questionnaire (EAQ), which samples a broad range of activities relevant to older adults’ lives (maintenance of self and property, social, leisure, religious, and creative activities) [75]. Lastly, the Social Disengagement Inventory (SDI) will be used to measure how participants interact and engage with their social environment [76].

Brain activity will be measured (Pre- and Post-Training) using functional near infrared spectroscopy (fNIRS) at Concordia’s PERFORM Centre. The working brain is in constant need of supply of glucose and oxygen for efficient functioning. As such, levels of oxygenated hemoglobin (HbO) and deoxygenated hemoglobin (HbR) in the brain can be used as neurobiological indicators of cortical activation. Increased brain activation leads to increased blood volume and blood flow, resulting in an increase in HbO and a decrease in HbR. Conversely, decreased brain activation leads to decreased blood volume and blood flow, resulting in a decrease in HbO and an increase in HbR. Functional near infrared spectroscopy provides a non-invasive measure of HbO and HbR fluctuations in the cerebral cortex with high temporal resolution [77]. A mobile (wireless/Bluetooth) fNIRS device will be used to allow participants to freely complete the experimental task while walking (Artinis Brite MKIII, Netherlands). Light optode placement will follow a 24-channel frontal template provided by the analysis software OxySoft (Version 3.3.30). Data pre-processing involving the visual inspection of motion artifacts, detection of bad channels, Modified Beer-Lambert Law (MBLL) conversion, and band pass filtering (0.005 Hz-0.1 Hz), will be conducted using MATLAB (Version R2021b) and the open-source application Brainstorm [78]. Additionally, all trials will be normalized to baseline, which will be taken during a quiet standing condition prior to each trial. A single HbO activation average will be computed for each participant for each trial type (i.e., single-task walking, single-task 2-back, and dual-task). HbO change scores will then be derived to compare Pre- and Post-Training cortical activation levels.

### Study procedure

Prior to any in-person visit, a telephone screening will be conducted to determine a participant’s initial eligibility to participate in the study (i.e., will gather demographic information and a basic medical history, as well as the participant’s comfort level using a computer or tablet). Eligible participants will be asked to come into Concordia University’s Loyola Campus (Montreal location) or KITE-Toronto Rehabilitation Institute, University Health Network (University Centre location) to provide written consent, be further screened using a more in-depth health history interview, and be assessed on various cognitive and sensory measures, including pure-tone audiometry, CDTT, MoCA, Pelli-Robson Contrast Sensitivity, RAVLT, Coding, Digit Span, Trail Making Test A & B, Letter-Number-Sequencing, and Color Word Inference Test (Pre-Training Session 1). Testing will take place in a quiet, well-illuminated room. If deemed eligible, participants will be asked to come into Concordia University’s PERFORM Centre (Montreal location) or KITE-Toronto Rehabilitation Institute, University Health Network (University Centre) to assess our primary outcome measure (i.e., cognitive-motor dual-tasking) and other measures including the ETDRS and Mini-BESTest (Pre-Training Session 2). Participants will also be asked to complete a series of questionnaires online between Pre-Training Sessions 1 and 2 (i.e., LSEQ, ABC, EAQ, FFQ, HHIE-S, SDI). Participants will then be randomized into either the executive function training group or the wait-list control group. The executive function training group will receive a virtual tutorial session on how to use the at-home cognitive training program. Participants will then undergo either 12 weeks of cognitive training or will continue their life as usual (wait-list control group). Both groups will be called once a week to keep track of any changes in lifestyle, stress, energy levels or any other important life events. The executive function training group will also be asked about their training that week (e.g., if they are having any difficulty with the training or need further clarification, if they are noticing any progress/improvements, if they are experiencing any technical issues, if they missed a session). Following the 12-week period, all participants will be invited back to complete the same sensory, cognitive, and motor assessments that they completed at baseline (Post-Training Session 1 and Post-Training Session 2). Participants will also complete the LSEQ, ABC, and FFQ questionnaires again to measure changes in subjective hearing, mobility, and cognition, respectively. An overview of the study procedure across each testing site is shown in Fig. 2.

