### Waitlist control group

Participants randomized to the wait-list control group will complete both the Pre- and Post-Training assessments but will not partake in any form of cognitive training during the 12-week period. Weekly phone calls will ensure that participants are maintaining a consistent lifestyle and that they are not starting any other cognitive training programs. The weekly phone calls will also allow for a similar level of social interaction amongst the research personnel and the participants across the wait-list control and training groups in order to control for this possible confound. Upon completing the study, the wait-list control group will be offered the materials for the at-home executive function training program, and researchers will be available to offer assistance if needed.

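### The weekly calls match contact in frequency only: the unblinded training arm alone is asked whether it notices improvement, which can add expectancy in one arm

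*Protocol article*

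**What the plan says.** All references are to the Protocol article.

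- **Study procedure, common content:** "Both groups will be called once a week to keep track of any changes in lifestyle, stress, energy levels", together with other life events.
- **Study procedure, training arm only:** "The executive function training group will also be asked about their training that week". Among the examples listed there are "if they are having any difficulty with the training or need further clarification, if they are noticing any progress/improvements"; technical problems and missed sessions complete the list. This arm alone also has a virtual tutorial.
- **Waitlist control group:** the calls check that lifestyle is stable and that no other cognitive training has begun. A further stated aim is that they "allow for a similar level of social interaction amongst the research personnel and the participants across the wait-list control and training groups". The article gives the purpose of this as follows: "in order to control for this possible confound".
- **Blinding:** participants know their allocation after baseline. The staff who make the calls are to differ from those who carry out the post-training evaluations.
- **At-home executive function training group:** reaction time and accuracy are recorded for all three modules, and a feedback graph follows each session.
- **Study procedure, after training:** "Participants will also complete the LSEQ, ABC, and FFQ questionnaires again to measure changes in subjective hearing, mobility, and cognition, respectively".

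**The concern.** The article names a confound and states that the weekly calls control for it. The described content of the calls gives that statement only partial support. One arm is asked only about daily life. The other is asked about daily life and also whether it sees itself getting better.

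The progress question differs in kind from the other training questions. Asking about difficulties, technical faults and missed sessions supports unsupervised home training. Asking about improvement supports nothing that the program does not already record. It invites participants who know they are being trained to look for benefit, and it comes from study staff.

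At stake is the reading of a between-arm difference. LSEQ and ABC are ratings of confidence or self-efficacy, and FFQ rates one's own memory. Participants complete these questionnaires online, so evaluator blinding gives them no protection. Performance scores also depend on effort. Under Planned analyses, a significant Time by Training Group interaction in any primary outcome counts as preliminary evidence of training efficacy, so a non-specific difference would be credited to the training.

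**Working it through.** The plan gives no figure to reproduce, so the check sets the sections side by side.

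**1. Are the calls alike?**

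| Feature | Training arm | Wait-list arm | Source |
|---|---|---|---|
| Call frequency | weekly | weekly | Study procedure |
| Lifestyle, stress, energy, life events | yes | yes | Study procedure |
| Difficulties, technical faults, missed sessions | yes | no | Study procedure |
| Noticed progress or improvement | yes | no | Study procedure |
| Tutorial | yes | no | Study procedure |
| Feedback graph after each session | yes | no | At-home training group |
| Knows own arm | yes | yes | Blinding |

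Frequency is matched and content is not. Call length is not given for either arm.

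**2. Is the progress question needed?** Training is planned as 3 sessions × 12 weeks = 36 sessions, with performance recorded and a graph shown after each. Progress on the tasks is therefore already known to the program and to the participant.

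**3. Which outcomes are exposed?**
- LSEQ, ABC and FFQ: self-rated, completed online, repeated after training by participants who know their arm. Most exposed.
- Accuracy, reaction time, gait timing and posture: instrument-measured or scored by rule, but dependent on effort. Less exposed.
- Dual-task cost, (S − D)/S × 100, with S the single-task and D the dual-task score: if effort scales both by the same factor c, then (cS − cD)/(cS) = (S − D)/S and the cost is unchanged. Effort that changes only the dual-task score does not cancel.

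**4. What would a non-specific shift do?** The documents give no size, so the shifts below are assumptions. They stand for all non-specific effects together, not the calls alone. Take a two-sided 0.05 t-test on change scores, which is the Time by Training Group test without covariates. With n per arm, no true training effect and a shift of d SDs of the change score, df = 2n − 2 and the noncentrality is d × √(n/2). With 60 per site and equal allocation, n = 30, or 27 after 10% attrition (30 × 0.9).

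| Assumed shift d | Noncentrality, n = 30 | P(reject), n = 30 | P(reject), n = 27 |
|---|---|---|---|
| 0 | 0 | 5.0% | 5.0% |
| 0.1 | 0.39 | 6.7% | 6.5% |
| 0.2 | 0.77 | 11.9% | 11.1% |
| 0.3 | 1.16 | 20.8% | 19.1% |

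These are per-outcome probabilities. They show why an avoidable one-arm prompt is worth removing; they do not size this point.

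**The case against.** The other side has a good deal to say.

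- **The article claims similar interaction, not equal interaction.** This stands. Weekly calls in both arms do give partial control of contact, and an untreated arm cannot be asked about training it is not doing. What goes too far is the clause on controlling the confound.
- **The progress question is one item in a list of examples.** This stands. It may refer to progress on the training tasks, and the actual script is not shown. The wording does not limit it to the tasks, however, and the article itself offers it as typical content.
- **The most exposed outcomes are secondary.** This stands. No hypothesis under Planned analyses rests on LSEQ, ABC or FFQ. The primary measures are instrument-based or scored by rule, evaluators are meant to be blind, and treadmill speed is held constant across conditions. These features reduce the exposure of the primary outcomes but do not remove differences in effort.
- **Expectancy arises anyway.** This stands. An openly known wait-list comparator, the tutorial and the feedback graph all contribute, and the share due to the calls cannot be isolated. That limits what the change can achieve, but it does not justify keeping a prompt that serves no purpose in delivery.

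A reader might infer more: that the calls demonstrably bias the results towards training, that training-arm calls are longer, or that each trained participant receives 12 improvement prompts. The documents support none of these. They give no call length and no fixed script. Nothing in them establishes the direction of an effect, and questions about difficulties and missed sessions could even lower self-ratings.

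**Conclusion.** The point holds in a limited form. The calls are matched in frequency but not in content, so they control only partly for contact and not for expectancy. The progress question is an avoidable one-arm prompt that can affect self-ratings and, less so, effort-dependent scores.

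The size is unknown. The rejection probabilities shown rest on assumed shifts, 30 or 27 participants per arm at one site and no true training effect, and they cover every non-specific source. Bias is possible here, not demonstrated. The change reduces one source of expectancy and leaves the wait-list comparator, tutorial and feedback graph in place. It is worth making because it is cheap, not because the calls alone undermine the trial.

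**What to change.** 1. Remove the question on progress or improvement from the weekly calls, or ask it only after Post-Training Session 2 and the post-training questionnaires are complete.
2. Use the same script in both arms for lifestyle, stress, energy and life events.
3. Keep questions on difficulty, technical faults and missed sessions brief and neutral within the existing call. A separate help line or message service would add a further training-only contact and widen the imbalance.
4. Under Waitlist control group, say that call frequency is matched between arms, that this controls only partly for contact, and that it does not control for expectancy.

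The cost is a revised call script and one reworded sentence, with no added visits or contacts. The downside is the loss of a weekly qualitative progress note.
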